### Study Design

A randomised controlled trial design was undertaken. Eligible mothers were those living in the 2168 postcode area of Sydney, New South Wales (NSW) and identified as at-risk through the responses given by the expectant mother at the standardised psychosocial assessment [15] conducted by antenatal clinic midwives for all mothers booking into a large teaching hospital in South Western Sydney for confinement. Women were classified as at-risk when seen in the hospital antenatal clinic if they had any one of a number of factors present that have been shown to be risk factors for poorer coping as a parent [15]. These were:

1) A positive response to any of 12 psychosocial questions routinely asked in the antenatal clinic. These questions assess expected lack of practical and emotional support, stressors in the past 12 months, personality, mental health, history of abuse in the mother's childhood, and family violence (see Matthey et al. [15], for details of these questions and responses deemed to indicate 'at-risk' status). In addition, the presence of any one of the following also meant the woman was classified as 'at-risk': maternal age under 19 years, late antenatal care after 20 weeks gestation, and current substance misuse.

2) Current probable distress. This was assessed using the Edinburgh Depression Scale (EDS) [16]. An EDS score of 10 or more may approximate the subgroups labelled in other trials as 'psychologically vulnerable' or 'low psychological resources' [17]. This score was used by the hospital's antenatal clinic to be inclusive of all women with probable distress and is lower than the validated antenatal score of 13 or more (for minor depression) or 15 or more (for major depression) [15,18,19]. There is an increasing body of evidence from both animal and human studies that psychosocial distress in pregnancy has significant impacts on developmental and behavioural outcomes for children [20], and health in later life [21].

Mothers who required the use of an interpreter or who did not have a phone were ineligible to participate.

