**Figure 1 F1:**
[figure not shown]
**Measurements**.

Study measures were obtained by interviewer administered questionnaire antenatally and at 1, 12, and 24 months postpartum. In addition, women were telephoned at 6 months postpartum to maintain contact and encourage study retention. Antenatal, 12 month and 24 month questionnaires were administered by face-to-face interview and included observation measures. Interviewer administration was chosen due to low literacy rates within the study population. At approximately 18 and 30 months standardised developmental assessments and observation of parent-child interaction were conducted and videotaped either at the hospital, community health facility or the family home. All questionnaires and standardised testing were administered in English.

With consent, hospital clinical and community service use data were obtained for the mother and her child from the hospital inpatient and outpatient records and community health records for the period from birth up to 24 months postpartum. These data are available for the whole sample and is not dependent on participant retention.

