### Statistical analyses

All data analysis will be carried out according to a pre-established analysis plan. The primary analysis will be intention-to-treat. Two sided significance tests will be used. Power calculations will be conducted on all parametric analyses. Only findings with power > 80%, CI = 95% and ά < 0.05 will be determined to be statistically significant. Differences between the intervention and comparison groups in the proportion of mothers using nursing, medical, other health, parental support and child care services will be analysed using contingency tables. Descriptive analyses will be undertaken of critical events such as death or child removal as the incidence of these events is low in the Australian population. Impact and outcome data collected at multiple time points will allow imputation of missing data for participants who did not complete every data point using appropriate techniques [24,25]. Child development and parent-child interaction measures, and quality of the home environment (HOME inventory) will be analysed cross-sectionally at each collection point. All other impact and outcomes measures will be analysed cross-sectionally at 1, 12 and 24 months, to estimate the prevalence of each impact and outcome, their association with demographic and risk factors, and differences between the intervention and comparison groups using contingency tables for non-parametric data and t-tests for parametric data. Longitudinal analyses will then be undertaken to compare differences in outcomes over time between the intervention and comparison groups using Repeated Measures ANOVA for parametric data and Friedmans two-way ANOVA for non-parametric data.

A priori subgroup analyses will be conducted using General Linear Modelling to assess differences between the intervention and comparison groups in impact and outcomes for: first-time mothers compared with mothers with two or more children; Australian born mothers compared with mothers born overseas; mothers with only one risk factor compared with mothers with multiple risks at the time of recruitment antenatally; and mothers with lower psychosocial resources due to probable distress at the time of recruitment (EDS score of 10 or more) compared with mothers with higher psychosocial resources for parenting (EDS score of 9 or less).

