### Sample Description

During the recruitment period 847 pregnant women from the 2168 postcode area were identified. Of these women, 509 were excluded from the study because they did not meet the eligibility criteria: no risk factors (n = 338), required an interpreter (n = 98), no telephone (n = 33), no data provided to the SRO (n = 40). From the eligible population (n = 338), another 130 were excluded for reasons such as refusal to participate, non-contactable or maternal and/or foetal death.

Two hundred and eight (208) women were recruited to participate in the study and were randomly assigned to the intervention (n = 111) and comparison group (n = 97). The baseline demographic and risk characteristics of the trial groups are detailed in Tables 1 and 2. At an average of 27.7 years, the mothers in the sample were slightly younger than mothers who gave birth in NSW in 2005 (29.9 years), however, their age was similar to mothers from the most disadvantaged quintile (28.0 years) [23]. A considerably larger proportion of women in the sample were born in an overseas country (49.0%), most of whom were born in a non-English speaking country, compared with mothers birthing in NSW in 2005 (27.9% born overseas) [31].

**Table 1 T1:** Baseline maternal demographic characteristics of trial groups

**Characteristic**	**Intervention Group (n = 111)**	**Comparison Group (n = 97)**
Mean age ± SD	27.6 ± 6.7	27.7 ± 5.9

Parity, n (%)		

0	31 (27.9)	34 (35.1)

≥ 1	80 (72.1)	63 (64.9)

Country of birth, n (%)		

Australia	56 (50.5)	50 (51.5)

Overseas	55 (49.5)	47 (48.5)

Marital status, n (%)*		

Married/living with partner	87 (80.6)	79 (84.9)

Single/separated/divorced	21 (19.4)	14 (15.4)

Level of education, n (%)†		

High school/vocational	88 (83.0)	74 (80.4)

Degree or higher	18 (17.0)	18 (19.6)

Main source of household income, n (%)†		

Full or part-time wages	73 (68.9)	66 (72.5)

Benefit or pension	33 (31.1)	25 (27.5)

Housing tenure, n (%)§		

Own or purchasing	47 (46.1)	43 (50.6)

Renting or other	55 (53.9)	42 (49.4)

* Seven women did not disclose their marital status

† Eleven women did not disclose their level of education or source of income

§ Twenty one women did not disclose their housing tenure

**Table 2 T2:** Baseline maternal risk characteristics of trial groups

**Characteristic**	**Intervention Group (n = 111)**	**Comparison Group (n = 97)**
Age < 19 years, n (%)	7 (6.3)	7 (7.2)

Unsupported parent, n (%)	4 (3.6)	0 (0.0)

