A particular strength of the study was recruitment of women through the public hospital antenatal clinic, using a population base for recruitment. In NSW most women (74.4%) utilise the public hospital for birthing services [31], and the proportion is likely to be higher for women in disadvantaged communities. There is evidence that home visiting interventions that are based in population level recruitment are more likely to be successful than those based on referral of clients [32]. Further, the intervention was based in the local primary health care service and utilised resources and infrastructure available in the local area rather than using a separate, specialised research-based team, making this a trial of a program that is directly replicable at the service level.

Women whose lack of English-language proficiency required the use of an interpreter were excluded from the study, and this may limit the generalisability of the study. The study did, however, include a large proportion of women from non-English speaking backgrounds, facilitated by the use of interviewer administered questionnaires that required only English language ability that is sufficient to understand simple verbal questions, rather than English language proficiency or literacy.

The most significant limitation of the study is the low rates of participation at each data point, which may reduce the power of the study to detect small and moderate effects of the intervention. The collection of the same data items at multiple data points should facilitate imputation of values for data points missed by individual participants and minimise the impact of lower participation, however, this will remain a limitation for measures analysed cross-sectionally.

The MECSH trial has been designed to provide Australian evidence of effective intervention to improve the health and development of children living in disadvantaged communities who are at-risk of poorer outcomes. It is envisaged that the comprehensive ecological base of the intervention and research measures, and the location of the trial within existing local services, will provide evidence of best practice to reduce inequalities through early childhood intervention.

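### English-only child testing may add avoidable variance to the Bayley mental score; adjusting the between-arm comparison for maternal country of birth would recover some of it at no cost

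*Protocol article*

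**What the plan says.** All places are in the protocol article.

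- **Data collection (text below Figure 1):** "At approximately 18 and 30 months standardised developmental assessments and observation of parent-child interaction were conducted", and "All questionnaires and standardised testing were administered in English".
- **Study Design:** the language criterion applies to the mother: "Mothers who required the use of an interpreter or who did not have a phone were ineligible to participate". The text shown does not mention the child's home language.
- **Sample Description:** a considerably larger proportion of the sample than of NSW mothers was "born in an overseas country (49.0%), most of whom were born in a non-English speaking country". Table 1 gives 55 of 111 in the intervention group and 47 of 97 in the comparison group.
- **Sample size:** the Bayley mental scale is one of the outcomes for which 75 per group is said to give power of 0.80 at an effect size of 0.5 or larger.
- **Statistical analyses:** child development is to be analysed cross-sectionally at each collection point, and no covariate is named for that comparison. General Linear Modelling will be used "to assess differences between the intervention and comparison groups in impact and outcomes for" several subgroup pairs, one of them "Australian born mothers compared with mothers born overseas".
- **Discussion:** the inclusion of women from non-English-speaking backgrounds is credited to questionnaires that "required only English language ability that is sufficient to understand simple verbal questions, rather than English language proficiency or literacy".

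**The concern.** The Discussion's argument fits a mother answering simple spoken questions. It does not reach a child aged 18 or 30 months taking a standardised test in English who may hear mainly another language at home. For such children the mental score may reflect exposure to English as well as development.

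Two things are then at stake. First, differences in language background between families would add spread to the score that has nothing to do with the programme, and an unadjusted comparison would carry it as noise. Secondly, a difference in effect between the birthplace subgroups on this score could come partly from the test rather than from the programme.

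**Working it through.** **Inputs from the article.** Overseas-born 55/111 and 47/97; Australian-born 56/111 and 50/97 (Table 1). Effect size 0.5 and 75 per group (Sample size). Two-sided tests at 5% (Statistical analyses). Retention 62.5% at 30 months (Discussion).

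**Assumed inputs.** SD of 1 within a language group; language-related gap δ of 0.5 to 1 SD; share f of overseas-born mothers from non-English-speaking countries of 0.6 to 1.0 (the article says only that it is most of them).

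**1. The article's own figures.** (55 + 47)/(111 + 97) = 102/208 = 49.0%, as stated. Power = Φ(d√(n/2) − 1.96) = Φ(0.5 × 6.124 − 1.96) = Φ(1.102) = 0.865; the t-test version gives 0.860. Power of 0.80 needs only 63 to 64 per group, so the stated 0.80 is conservative.

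**2. Bias in the overall comparison.** A shift of −1 SD in every overseas-born family moves the arm difference by −1 × (55/111 − 47/97) = −0.011 SD, which is negligible.

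**3. Added variance.** With a share q of children affected, the SD becomes √(1 + q(1 − q)δ²). For f = 1, q = 0.49 and q(1 − q) = 0.250:

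| δ | SD | d = 0.5/SD | Power, 75 per group |
|---|---|---|---|
| 0 | 1.000 | 0.500 | 0.865 |
| 0.5 | 1.031 | 0.485 | 0.844 |
| 1.0 | 1.118 | 0.447 | 0.782 |

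For f = 0.6, q = 0.294 and q(1 − q) = 0.208; power is 0.847 at δ = 0.5 and 0.796 at δ = 1. At 62.5% retention, 0.625 × 208 = 130 women, or about 65 per group; the same formula with f = 1 gives 0.81, 0.79 and 0.72 for δ = 0, 0.5 and 1.

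**4. What adjustment recovers.** A covariate that separates English-speaking from non-English-speaking countries of birth removes the whole of this variance in the model above. The coarser Australia v overseas split leaves 0.49 × f(1 − f)δ². At f = 0.6 and δ = 1 that is 0.118 of the original 0.208, so about 43% is recovered and power at 75 per group rises from 0.796 to Φ(0.5/√1.118 × 6.124 − 1.96) = 0.825. At f = 1 the coarse split recovers everything.

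**5. The birthplace contrast.** It is a difference of two between-arm differences. A uniform shift from 0 to −1 SD in the overseas-born leaves the simulated contrast at about 0. If instead the English test registers a fraction c of a true 0.5 SD gain in the overseas-born, the contrast is 0.5(c − 1): −0.05, −0.10, −0.15 and −0.25 SD for c = 0.9, 0.8, 0.7 and 0.5. The standard error is √(1/56 + 1/50 + 1/55 + 1/47) = 0.28 SD with all 208 women, and 0.28/√0.625 = 0.35 SD at 62.5% retention. The interaction detectable with 80% power is 2.80 times these, 0.78 and 0.99 SD.

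**The case against.** A reader might infer that the Australian-born v overseas-born contrast on the mental score cannot be read as a difference in programme effect at all. The documents do not support that. The planned analysis compares randomised arms within each birthplace group, not raw scores between the groups, and measurement was identical in both arms. Distortion needs something more: lower sensitivity to gains, a floor effect, or a programme that changes English exposure differently in the two groups. Each is conceivable and none is shown. Even the assumed artefact of 0.05 to 0.25 SD is smaller than the contrast's standard error.

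A reader might also infer that the main effect is diluted. That too requires the test to miss part of the gain, and no figure in the article says how much.

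Three further points count against a strong claim. Birthplace is a crude proxy for the language a child hears: some overseas-born mothers come from English-speaking countries, and 98 women who needed an interpreter were excluded. Figure 1 is not shown, so whether home language was recorded, and exactly which scales were given, cannot be determined. The article refers to a pre-established analysis plan that is not shown and might already contain covariates.

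These points stand, and they limit this to a matter of precision and interpretation. They do not remove the mismatch between the simple-English argument and child testing, or the gain available from a baseline variable already in hand.

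**Conclusion.** The point holds as an inexpensive improvement, not as an error that threatens the trial's conclusion. English-only child testing does not bias the overall randomised comparison. It may add avoidable variance to the Bayley mental score: about 2 percentage points of power at 75 per group for a gap of 0.5 SD, and about 8 for a gap of 1 SD, the latter taking planned power just below the stated 0.80. These sizes rest on the assumed gap, on an SD of 1 within language groups, and on nearly all overseas-born mothers coming from non-English-speaking countries; at a share of 60% the losses are about 2 and 7 points. The birthplace contrast remains a legitimate comparison of programme effects. On this score it needs a caution, because test sensitivity could contribute to it by an unknown amount in an unknown direction.

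**What to change.** In Statistical analyses, state that the between-arm difference in the Bayley mental score at each collection point will be estimated with a linear model containing treatment group and maternal country of birth as a baseline covariate. Use English-speaking v non-English-speaking country where that is recorded; otherwise use Australia v overseas, which recovers less of the variance.

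Keep the planned Australian-born v overseas-born contrast, and add one sentence saying that an interaction on this score could partly reflect differing sensitivity of an English-language test and should be read with caution.

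The cost is a few lines of analysis-plan text and one degree of freedom. Country of birth comes from the routine data collections, and Table 1 accounts for all 208 women (56 + 50 + 55 + 47), so no new data are needed. Adjustment addresses added variance only; it does not cure differing sensitivity of the test, which is why the caution is needed as well.

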### Data accuracy

Interviewers were trained in the sensitive and standard administration of the measures. Trained registered child psychologists conducted the standardised testing. The research team met regularly to review interview techniques and ensure consistency of administration. One in ten standardised tests was reviewed by an independent psychologist. All data were checked to ensure accuracy and consistency of data entry.

### Data entry and security

All data were entered into electronic databases developed by the SRO and RA. Each participant was given a record number. All data were entered using record number identification only and are stored in password protected files under the responsibility of the SRO in accordance with the requirements of the National Health and Medical Research Council and the *Privacy Act *1988. Identification information is stored in a separate password protected file.

### Sample size

Funding allowed three nurses to be employed to deliver the intervention, each with a maximum caseload of 25 mothers (in accordance with NSW Department of Health guidelines). Hence, 75 families could be receiving intervention at any one time. Previous randomised controlled trials reported in the literature have had a median number of subjects of 65 per group (range 9–347). A sample size of 75 subjects per group has power of 0.80 at the 95% level to detect effect sizes of 0.5 or larger for the HOME Inventory, Bayley Scale of Mental Development and maternal health (SF-12), and detect differences of less than 22% in the rates of immunisation, child injury and breast-feeding. In systematic reviews of home visiting conducted by Elkan [12] and MacLeod [5] effects of at least these sizes were found in the HOME Inventory; a meta-analysis of trials using the Bayley Scales of Mental and Motor Development showed an overall effect size of 0.17, however, effect sizes were larger (up to 0.5 for mental development and 0.4 for motor development) in studies that assessed development at 12 months or later; the pooled odds ratio for immunisation and breastfeeding at 3 months were 1.40 and 1.34 respectively; the pooled odds ratio for reduction in child injury in studies aimed at improving a range of child and maternal health outcomes was 0.76; significant change in depression and stress scores were reported in studies using EDS and the Parenting Stress Index. Trials with fewer than 50 subjects have shown significant intervention effects in the quality of the home environment measured using the HOME inventory, child mental development measured using the Bayley Scale of Infant Mental Development, immunisation rates, possible maternal depression measured using the EDS, parenting stress measured using the Abidin Parenting Stress Index, and transition to solids [12]. Recruitment took place over the period February 2003 to March 2005. This allowed a planned recruitment of 90 subjects per group whilst maintaining the maximum intervention caseload of 75, to allow for a proposed 15% loss to follow-up.

### Randomisation

A permuted block design was used to randomly allocate mothers to the intervention or comparison group. Blocks were based on the weekly intake of eligible clients at the antenatal clinic and varied in size from zero to six. Within each weekly block, a random selection of cases to receive intervention was made using SPSS. An allocation ratio of 1:1 was primarily used, however, this was varied to 3:2 from November 2004 in order to maintain the intervention caseload of 75 families. Randomisation was conducted by the SRO. Allocation was concealed from all nurses and other research staff until after mothers consented to participate in the study and baseline data had been collected by the RA blinded to the allocation.

### Blinding

In this trial, blinding of participants and intervention nurses was not possible. Outcome data was collected by a RA who was initially blinded to group allocation, however, commonly participants would reveal their group allocation during the data collection process. Standardised testing was undertaken by child psychologists who were blinded to group allocation.

### Statistical analyses

All data analysis will be carried out according to a pre-established analysis plan. The primary analysis will be intention-to-treat. Two sided significance tests will be used. Power calculations will be conducted on all parametric analyses. Only findings with power > 80%, CI = 95% and ά < 0.05 will be determined to be statistically significant. Differences between the intervention and comparison groups in the proportion of mothers using nursing, medical, other health, parental support and child care services will be analysed using contingency tables. Descriptive analyses will be undertaken of critical events such as death or child removal as the incidence of these events is low in the Australian population. Impact and outcome data collected at multiple time points will allow imputation of missing data for participants who did not complete every data point using appropriate techniques [24,25]. Child development and parent-child interaction measures, and quality of the home environment (HOME inventory) will be analysed cross-sectionally at each collection point. All other impact and outcomes measures will be analysed cross-sectionally at 1, 12 and 24 months, to estimate the prevalence of each impact and outcome, their association with demographic and risk factors, and differences between the intervention and comparison groups using contingency tables for non-parametric data and t-tests for parametric data. Longitudinal analyses will then be undertaken to compare differences in outcomes over time between the intervention and comparison groups using Repeated Measures ANOVA for parametric data and Friedmans two-way ANOVA for non-parametric data.

A priori subgroup analyses will be conducted using General Linear Modelling to assess differences between the intervention and comparison groups in impact and outcomes for: first-time mothers compared with mothers with two or more children; Australian born mothers compared with mothers born overseas; mothers with only one risk factor compared with mothers with multiple risks at the time of recruitment antenatally; and mothers with lower psychosocial resources due to probable distress at the time of recruitment (EDS score of 10 or more) compared with mothers with higher psychosocial resources for parenting (EDS score of 9 or less).

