## Discussion

This study, the first Australian study to measure the impact of a SNHV program commencing antenatally, continuing to child-age 2 years, successfully recruited a cohort of women at-risk of poorer parenting outcomes from a disadvantaged community. The number of women to participate in the study was limited to the maximum caseload of the intervention nurses and a matching number of comparison women. Rates of retention were poorer than predicted, with 62.5 percent retained at 30 months. The rates of retention at 12 and 24 months (86% and 74% respectively), however, compare somewhat favourably with those reported in previous randomised control trials [12], which had a mean retention rate of 84 percent for studies measuring outcomes up to 12 months and 77 percent for studies measuring outcomes up to 24 months.

The rates of participation of women in data collection at each data point, however, ranged from 67.7 percent at 1 month postnatal to 51.4 percent at 24 months postnatal. Participation by the intervention group was more complete than the comparison group, with the comparison group having lower participation at each data point, despite similar rates of active follow-up. Importantly, however, retention and participation rates were not significantly different for the intervention and comparison groups at any time point, and hospital clinical and community service use data will be available for the whole cohort.

Women who presented for antenatal care after 20 weeks pregnancy were particularly difficult to retain in the study, and this may be indicative of a group that is difficult to engage in service delivery and hence also service based research. There is evidence that women with other risk factors, including those with multiple risks or higher particular risks, such as domestic violence or drug or alcohol use, were retained at the same rate as their relatively lower risk counterparts, with one group of women, those who were abused themselves as children, more likely to participate throughout the study than women who were not abused.

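### Making power above 80% a condition of statistical significance either lowers the 0.05 threshold to about 0.0055 or blocks 24-month complete-case t-tests whatever their p-value

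*Protocol article*

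**What the plan says.** The Statistical analyses section of the protocol article first fixes the tests: "Two sided significance tests will be used". It then says "Power calculations will be conducted on all parametric analyses. Only findings with power > 80%, CI = 95", and the second of these sentences, which sets the decision rule, reads in full: "Only findings with power > 80%, CI = 95% and ά < 0.05 will be determined to be statistically significant". The rule is forward-looking and attached to findings, so it is separate from the design calculation. It does not say whether power is to be computed at the observed effect, the planned effect or some other value.

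The design calculation is in the Sample size section: "A sample size of 75 subjects per group has power of 0.80 at the 95% level to detect effect sizes of 0.5 or larger", with the HOME Inventory, the Bayley mental scale and the SF-12 named as the measures. Recruitment was raised to 90 per group "to allow for a proposed 15% loss to follow-up". The Discussion gives achieved participation as low as "51.4 percent at 24 months postnatal".

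**The concern.** Power is a property of a design at a stated effect. It is not evidence about a result already in hand. Once it is a condition of significance, the operating characteristics of the test are no longer those of a two-sided 0.05 test, and the 0.80 power claimed under Sample size may no longer apply. The rule governs which parametric results the trial reports as significant, so a real benefit of home visiting could be reported as not significant although its p-value is well below 0.05. Effects that do pass a stricter filter are also more exaggerated on average.

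**Working it through.** **Inputs.** Two-sided alpha 0.05 and the power condition of 80% (Statistical analyses). 75 per group and effect d = 0.5 SD (Sample size). 111 and 97 randomised (Sample Description). 24-month participation 51.4% (Discussion), so 0.514 × 208 = 106.9, about 107 women. The split by arm is in a figure that is not shown. Applying 51.4% to each arm gives 57/50, which is an assumption; 53.5/53.5 is the balanced best case.

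**Formulas.** Standard error of d: se = √(1/n1 + 1/n2). Power of the t-test at effect d: the probability that a noncentral t with n1 + n2 − 2 degrees of freedom and noncentrality d/se exceeds the two-sided 5% critical value.

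**The plan's own figure.** At 75 per group, se = 0.1633, the noncentrality is 0.5/0.1633 = 3.06, and power is 0.86. The stated 0.80 is therefore conservative: 64 per group would be enough, and 75 per group reaches 0.80 at d = 0.46. This difference does not affect the point.

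**Reading 1: power at the observed effect.** In the normal approximation, observed power exceeds 0.80 when |z| > 1.960 + 0.842 = 2.802, which is p < 0.0051. A result at p = 0.05 has observed power of about 0.50, and one at p = 0.01 about 0.73, so both fail. The exact t-test version is:

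| n1/n2 | Observed d needed, p < 0.05 only | Observed d needed with power condition | Equivalent p | Chance of declaring true d = 0.5, p < 0.05 only | With power condition |
|---|---|---|---|---|---|
| 75/75 | 0.32 | 0.46 | 0.0055 | 0.86 | 0.60 |
| 57/50 | 0.38 | 0.55 | 0.0056 | 0.72 | 0.41 |
| 111/97 | 0.27 | 0.39 | 0.0054 | 0.95 | 0.78 |

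A balanced 53.5/53.5 split gives 0.73 and 0.41, the same conclusion as 57/50. Simulation with 100,000 trials per setting gave a type I error of 0.0053 (75/75) and 0.0058 (57/50) with the condition, against 0.050 without it.

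Exaggeration: for a true d of 0.3, the mean declared d is 0.45 with p < 0.05 alone and 0.55 with the condition at 75 per group. At 57/50 the figures are 0.52 and 0.65.

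**Reading 2: power at the planned 0.5 SD.** The condition now depends only on the number analysed:

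- 75 per group: power 0.86, so the condition is met and changes nothing.
- 107 women at 24 months: power 0.72 at 57/50 (0.7247 by noncentral t, 0.733 by normal approximation) and at most 0.73 if balanced. At least 64 per group (128 women) are needed, so a complete-case t-test fails the condition however small its p-value.
- 154 women (74% actively followed, 82/72 assumed): power 0.87. All 208: power 0.95. Both meet the condition.

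**The case against.** The strongest defence is that the rule is conservative. It does not raise the type I error, readers can still judge from estimates, p-values and intervals if these are reported, and an analysis plan not shown may define the reference effect. The first two statements are true but do not repair a rule that decides what is called significant. The third cannot rescue it on the two natural choices, the observed and the planned effect, because each does harm. Reading 2 would be harmless at 24 months only with a reference effect of about 0.55 SD or more, which is not the 0.5 the article plans for.

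Several stronger readings are tempting, and the article does not support them:

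- A reader might infer that every 24-month parametric result is barred. The bar arises only on reading 2 and only for complete-case t-tests on participants. The Data collection section says hospital and community record data exist for the whole sample. The Statistical analyses section plans imputation for measures taken repeatedly, and repeated-measures ANOVA, whose power is not the two-sample figure. The standardised developmental tests are at 18 and 30 months. The Discussion does concede that low participation remains a limitation for cross-sectional measures, so the complete-case bar is realistic.
- A reader might infer that any result at the planned effect size would fail. At 75 per group an observed d of 0.5 gives t = 3.06, p = 0.0026 and observed power 0.86, and it passes. With the 107 women (57/50) it gives p = 0.011 and fails on either reading.
- A reader might infer that true effects of 0.5 SD will be reported as null. On reading 1 this is a probability: 40% at 75 per group and 59% at 57/50, against 14% and about 28% without the condition.
- A reader might attribute all the exaggeration to the condition. At a true d of 0.3, part of it (0.30 to 0.45, or 0.30 to 0.52) is ordinary selection on p < 0.05 and would remain.
- A reader might infer that contingency-table outcomes can never qualify. The article ties the power calculations to parametric analyses and does not say that other results are barred. The scope is unclear, and no more than that can be claimed.

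**Conclusion.** The concern holds in this form: the power condition is a wrong decision rule as written, not a missing detail. On the observed-effect reading it turns a nominal 0.05 test into one at about 0.0055 at each sample size examined, imputed or not. It also brings the chance of detecting the planned effect at 75 per group to 0.60, below the 0.80 stated under Sample size. On the planned-effect reading it is harmless at the designed size but rules out significance for complete-case 24-month t-tests on about 107 women. The figures rest on equal-variance two-sample t-tests and, for 24 months, on the assumed 57/50 split. The Discussion says participation was lower in the comparison arm at each data point, so the true split may differ. The balanced split is the most favourable one for 107 women and leads to the same conclusion.

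**What to change.** Delete the power condition from the Statistical analyses section. Declare significance from the two-sided test at the stated alpha of 0.05, report every estimate with its 95% confidence interval, and use power only for planning. Where participation is low, the width of the interval already shows the loss of precision. The cost is one sentence in the analysis plan, with no further data, participants or computation.
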